#### Rejection criteria and termination standards

Rejection refers to excluding patients from the analysis if they (i) do not meet the inclusion criteria; (ii) withdraw written informed consent; (iii) do not receive follow-up care after selection for the trial; (iv) violate the terms of the trial (such as by improper use of the air purifiers, leading to effects that cannot be evaluated).

Termination refers to censoring patients who have met the inclusion criteria but who halted their participation in the trial. Data from these patients will be included in the final statistical analyses. Termination standards include (i) symptoms (e.g., sneezing, runny nose, nasal obstruction, or nose itching) that become severe; (ii) the occurrence of a serious event, or (iii) other health reasons sufficient to halt participation in the study.

#### Consent

Patients who are eligible for the study will be referred by their attending doctor, then the research coordinator will carry out the informed consent process. The research doctor will explain the details of the study to the patients, including its objectives, process, duration, and possible risks and benefits. And patients will sign the consent forms that they are entirely voluntary and their decision to participate in the study will not affect their future medical care. Recruited patients can withdraw from the study at any time for any personal reason. Patients also reserve the right for questioning about the study and the hesitant period. The burden of the intervention assessed will be charged by the research group.

## Follow-up

Upon completion of the 4-week treatment, patients will undergo a 4-week follow-up period. Research staff will continue to follow participants by telephone, short messaging via mobile telephone, or in the clinic. During the treatment period, follow-up will be conducted weekly. A record of symptom assessment and treatment compliance/changes will be maintained. If participants discontinue/deviate from the intervention protocols, research staff will record the reasons for the change. Such participants and their data will be excluded from the study.

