#### Inclusion and exclusion criteria

Inclusion criteria are confirmed AR and sensitivity to allergens from *Artemisia* pollen. Patients must be aged 18–65 years, provide written informed consent, volunteer to participate in this clinical trial, and complete the case report form and other records. Inclusion and exclusion criteria are detailed in Table 2.

**Table 2 Tab2:** Inclusion and exclusion criteria

Inclusion criteria	Exclusion criteria
Confirmed allergic rhinitis	Mental disorders
Sensitive to *Artemisia* pollen allergens	Systemic disease that the researchers consider to interfere with the study
Aged 18–65 years	Aged under 18 years or over 65 years
Provided informed consent and volunteered to participate in this clinical trial	Not cooperative during examination
Completed the case report form and other records	Employment changes leading to a possible loss to follow-up
	Dysgnosia or behavioral disorders
	The following conditions: nasal polyps, chronic sinusitis, severe nasal deviation, rhinitis medicamentosa, primary sleep disorders (> 1 night/week), obstructive sleep apnea, upper respiratory infection within 2 weeks prior to enrollment, or poorly controlled asthma
	Pregnant or may become pregnant, or lactating with a positive urine pregnancy test
	Drug abuse within the past 3 years
	Must sleep in different bed more than six times in 3 weeks or for more than 3 consecutive nights
	Smoked within the past 1 year
	Sensitive to indoor allergens such as dust mites and pet dander
	Other reasons, at the investigator’s discretion
	Refusal to continue the trial because of a poor curative effect
	Refusal to continue the trial for an unspecified reason
	Loss to follow-up because of a change of address or telephone number
	Loss to follow-up because of personal reasons

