### Statistical analyses

Statistical analyses will be carried out using SPSS v. 17.0 (IBM, Armonk, NY, USA) in the Clinical Evaluation Center of Southern Medical University (Guangzhou, China). Data will be described as the mean and standard deviation for normally distributed data, median and interquartile range for non-normally distributed data, and frequency and proportion for categorical data. All statistical inferences will be determined using two-sided tests. We will set a significance level of 0.05 and use 95% confidence intervals to measure the uncertainty of the estimate. Efficacy analyses will use last observation carried forward (LOCF) methodology to impute for cases not fully followed up during treatment. Pearson’s χ^2^ test will be used to compare the differences between the dropout rate and the dropout rate attributable to adverse events. Baseline data analyses (two sets) will include demographic indicators and general, primary, and secondary indicators before intervention. Measurement data will be compared using a paired *t*-test. For analyses of efficacy, for quantitative variables, comparisons between groups will be made by repeated measurement variance analysis and covariance analysis. For qualitative variables, comparisons between groups will be made using Pearson’s χ^2^ test, whereas central effects will be tested by a mixed-effects model. For rating variables, comparisons between groups will be made using the Kruskal-Wallis test. In terms of analyses of centre effects, the quantitative indicators will be tested by the general linear method, and the qualitative indicators will be tested by the Cochran-Mantel-Haenszel test methods. A logistic regression model will be used to evaluate and correct the rating variables.

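### The Follow-up section deletes everyone who discontinues or deviates, which conflicts with the termination rule and with LOCF, selects patients on outcome, and leaves the analysed population undetermined

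*Protocol article*

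**What the plan says.** Five sections of the protocol article bear on who is analysed.

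- **Follow-up.** The trigger is broad: "If participants discontinue/deviate from the intervention protocols, research staff will record the reasons for the change". The consequence follows at once: "Such participants and their data will be excluded from the study". No threshold or exception is given.
- **Rejection criteria and termination standards.** Termination covers eligible patients who halt because of severe symptoms, a serious event or other health reasons, and for them "Data from these patients will be included in the final statistical analyses". Rejection removes patients from the analysis on four grounds. Ground (i) is failing the inclusion criteria, and ground (iv) applies to those who "violate the terms of the trial (such as by improper use of the air purifiers, leading to effects that cannot be evaluated").
- **Statistical analyses.** "Efficacy analyses will use last observation carried forward (LOCF) methodology to impute for cases not fully followed up during treatment".
- **Inclusion and exclusion criteria, Table 2.** The exclusion column includes "Refusal to continue the trial because of a poor curative effect", refusal for an unspecified reason, and two loss-to-follow-up rows, one of which is "Loss to follow-up because of personal reasons". The inclusion column includes "Completed the case report form and other records".
- **Recruitment, screening, and enrollment.** Patients meeting any exclusion, rejection or termination item are not to be enrolled. Assignment to groups follows consent.

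**The concern.** A randomised comparison is protected only if membership of the analysis set does not depend on what happens after assignment. The Follow-up rule makes it depend on exactly that. A patient who stops because the purifier does not help has discontinued, so the rule removes that patient, with all VAS data, because of a poor response.

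The rule also cannot be followed together with the others. If the choice among them is left until the data are in, the primary VAS comparison can be run on different populations, each with some support in the text. The number affected is not trivial: the Sample size section predicts 30% dropout, which is 0.30 × 30 = 9 per group, or 18 of 60. A separate analysis plan could settle this only by overriding one of the protocol's own statements.

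**Working it through.** **1. The rules applied to the same patient**

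| Patient | Follow-up | Rejection/termination | Statistical analyses |
|---|---|---|---|
| Eligible, stops at day 14 for severe symptoms | Deleted | Included | LOCF from day 14 |
| Stops for poor effect, symptoms not severe | Deleted | Not named in either list | LOCF |
| Deviates, effect still evaluable | Deleted | Ground (iv) not met | Analysed |
| Misses a visit, intervention continued | Not clearly covered | Not named | LOCF |

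The first and third rows are direct contradictions. In the second, LOCF needs data that Follow-up removes. In the fourth the rules can coexist, so the conflict arises where the triggers overlap, not everywhere.

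**2. Timing in Table 2.** Refusal to continue and loss to follow-up can occur only after enrolment, yet the recruitment section applies them at enrolment. They cannot work as written.

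**3. The plan's own figure.** 21 / (1 − 0.30) = 30 per group, as stated. The base of 21 cannot be checked because no SD is given. Taking the difference as 1 VAS point, one-sided α = 0.05 and power 0.80: n = 2 × (1.645 + 0.842)² × SD². With SD = 1.28 this is 2 × 6.18 × 1.638 = 20.3, rounded up to 21. SD 1.28 is therefore an assumption consistent with the stated n. With all 30 per group kept, two-sided power is about 85%.

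**4. Size of the selection effect.** Further assumptions: 30 per group, a two-sided t-test, and a correlation r of 0.3 to 0.7 between poor outcome and exclusion. If a fraction p of an arm is removed from the poor end, the mean of those remaining rises by r × SD × h(p), where h(p) = φ(z_p)/(1 − p). Here h(0.10) = 0.195 and h(0.30) = 0.497. Error rates and power come from simulation.

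*Scenario A: one quitting rule in both arms, set so that 30% of control leave.*
- No true effect: both arms lose 30%, the shifts cancel, and type I error is about 5%.
- True benefit of 1 point: fewer active patients fall below the same threshold.
  - r = 0.3: 22.4% leave in active, h = 0.385. Estimate = 1 + 0.3 × 1.28 × (0.385 − 0.497) = 0.96. Power is about 69%.
  - r = 0.7: 14.2% leave in active, h = 0.262. Estimate = 1 + 0.7 × 1.28 × (0.262 − 0.497) = 0.79. Power is about 63%.
- Part of the lost power is plain loss of patients. Random loss leaving 26 and 21 would itself give about 74%. At r = 0.3 nearly all of the fall is of this kind.

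*Scenario B: exclusions of 10% in one arm and 30% in the other, for reasons other than effect.*
- Shift = r × 1.28 × (0.497 − 0.195): 0.12 at r = 0.3 and 0.27 at r = 0.7. The sign depends on which arm loses more.
- With no true effect, type I error is about 6% at r = 0.3 and about 12–13% at r = 0.7.
- With a true 1-point benefit, the estimate lies between about 0.73 and 1.27, depending on direction and r.

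**The case against.** The strongest reply is that the trial is double-blind with the same airflow in both arms, so without a true effect quitting for poor response should be equally common in each. That stands: scenario A gives no bias and about 5% type I error under the null. If the purifier works, this mechanism understates the benefit. A reader might infer that the rule makes false positives likely. The document does not support that, because it takes an arm imbalance with some other cause, and the predicted 30% dropout is one overall rate that says nothing about a split.

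Three other tempting readings also go too far.
- Table 2 might seem to order deletion of those who quit for poor effect. It does not: it misplaces such events among the eligibility criteria. Their deletion comes from Follow-up, and rejection (i) refers only to inclusion criteria.
- An incomplete case report form might seem certain to remove a randomised patient. Rejection (i), read literally with Table 2, allows this, but the prose above the table can be read as an undertaking to complete the records.
- Patients might be thought to have been removed already. Trial status reports only that 45 completed.

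None of this reconciles Follow-up with the termination rule or with LOCF.

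**Conclusion.** The contradiction is established from the text and needs no assumption: the sections give incompatible instructions for patients who stop or deviate, and the analysed population cannot be determined. Following the Follow-up rule as written selects on outcome. This must be fixed, because it decides who enters the primary comparison.

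The size and direction of any bias are not established. The ranges above depend on a back-solved SD, assumed exclusion rates and assumed correlations. The more natural mechanism, quitting for poor effect, costs power and shrinks a real benefit. Distortion in either direction, with type I error above 5%, requires exclusions that differ by arm for another reason.

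**What to change.** - Define the primary analysis set as all randomised patients in their assigned group, using all VAS data collected up to withdrawal. For those who withdraw consent, this is subject to the consent terms.
- Delete the last sentence of the Follow-up section's paragraph.
- Move the last four exclusion rows of Table 2 to a list of withdrawal reasons, and make completion of the case report form a consent undertaking.
- Align the recruitment section, the rejection and termination section and the LOCF statement with this set. The recruitment section should no longer apply post-enrolment events at enrolment.
- Limit rejection before analysis to ineligibility shown by pre-randomisation data and decided blind.
- Use deviations only for a supportive per-protocol analysis. The Design section says that the purifiers record operating hours, so a cut-off on those hours can be fixed before unblinding.
- Reconcile the termination, Follow-up and concomitant-care sections on whether permitted anti-allergy medication counts as a deviation, a termination or neither.
- If any patients have already been removed under the Follow-up rule, retain their data where consent allows.

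The cost is revised wording and the keeping of data already collected. The planned 60 patients do not change. Non-adherent patients may dilute the estimate slightly, and the per-protocol analysis will show by how much.

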### Intervention in the treatment group

The patients will operate an Atmosphere® air purifier (Amway China, Guangzhou, China) in their bedrooms. This air purifier contains a HEPA two-way filter (model number 101076CH) with an airflow velocity of 100/200 cubic feet/minute at a filtration rate of 6000/12,000 cubic feet/hour. This represents 4/8 air changes per hour in a typical bedroom measuring 15 × 12 × 8 ft. The air purifier will be placed in the bedroom of the patient. Instructions will be given for the units to be left running continuously. The patients must stay in their bedrooms at night for 4 weeks (> 8 h each day).

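### The Follow-up section excludes everyone who stops the intervention, with their data, while the termination rule keeps the data of those who stop for health reasons

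*Protocol article*

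**What the plan says.** Three places in the protocol article decide whether an incompletely treated or incompletely followed patient is analysed.

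- **Follow-up.** "If participants discontinue/deviate from the intervention protocols, research staff will record the reasons for the change". The next sentence gives the consequence: "Such participants and their data will be excluded from the study".
- **Rejection criteria and termination standards.** Rejected patients leave the analysis. Among the grounds are (iii), those who "do not receive follow-up care after selection for the trial", and (iv), those who "violate the terms of the trial (such as by improper use of the air purifiers, leading to effects that cannot be evaluated". Terminated patients are a separate class: eligible, but halted in the trial. The first listed ground is "symptoms (e.g., sneezing, runny nose, nasal obstruction, or nose itching) that become severe"; the others are a serious event and other sufficient health reasons. For this class the rule is "Data from these patients will be included in the final statistical analyses".
- **Statistical analyses.** "Efficacy analyses will use last observation carried forward (LOCF) methodology to impute for cases not fully followed up during treatment".

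The intervention from which a patient can depart is demanding. In both groups the unit is to run continuously, and for the treatment group the text adds: "The patients must stay in their bedrooms at night for 4 weeks (> 8 h each day". The control group has the same requirement.

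**The concern.** The Follow-up rule acts after randomisation and takes no account of why the patient stopped, although the reason is to be recorded. One foreseeable reason is that rhinitis symptoms became severe, and the primary VAS measures symptom severity and quality of life (Primary outcome measure). Dropping such patients selects on something close to the outcome. If these stops differ between the groups in number or kind, the remaining patients are no longer comparable as randomised.

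As the termination rule says to keep the same patients, two analysts working from this text could build different primary analysis sets and each cite the protocol.

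**Working it through.** No formula settles this point, so the rules are applied to four kinds of patient.

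1. **Eligible patient who stops the purifier and leaves in week 2 because symptoms became severe.** Follow-up: excluded with all data. Termination: data included. Last observation carried forward (LOCF): later values imputed, so the patient is kept. The first two instructions cannot both be followed. The result is the same for a serious event or another health reason.

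2. **Patient who departs from the regimen, for example by misusing the unit, but stays in the trial.** Follow-up: excluded. Rejection (iv): also excluded. The wording about effects that cannot be evaluated stands in a parenthesis introduced as an example, so it illustrates the clause and does not clearly limit it. The two sections largely agree here. The defect is that both remove a randomised patient because of behaviour after randomisation.

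3. **Patient who keeps running the unit but misses the day 21 or day 28 assessment.** Follow-up: not triggered, since the intervention was neither stopped nor departed from. LOCF: applies. The LOCF rule therefore has cases to act on even if the Follow-up rule is obeyed. It supports the reading that incompletely followed patients are kept, but it is not a second contradiction by itself.

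4. **Patient who stops the purifier for a reason unrelated to health but would still attend visits.** Follow-up: excluded. The listed termination grounds do not cover this patient, so the two rules do not clash, but a randomised patient and usable VAS data are again lost.

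**Direction of the bias.** Suppose more control patients than treated patients stop because symptoms became severe. Removing them makes the control group look better, and the benefit is understated. If more treated patients stop for that reason, the benefit is overstated. If stops are alike in number and kind, the effect may be small. The protocol gives nothing with which to choose between these.

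**Scale.** The Sample size section inflates 21 per group for 30% dropout: 21 / (1 − 0.30) = 30, which reproduces the stated 30. The predicted dropout is 0.30 × 30 = 9 per group, 18 of 60 in all. This is not the number affected by the conflict, because the dropouts are not split by reason and deviators who remain in the trial are not counted separately.

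**The case against.** - **The Follow-up sentence may be shorthand for the rejection class.** This would remove the conflict, but the text does not say so. Its trigger includes stopping, without qualification, and rejection (iv) does not cover a patient who stops for a health reason.
- **Follow-up may concern stopping the device, and termination leaving the trial.** A patient who leaves during the four treatment weeks also stops the intervention, so both rules still apply. The reading would also be odd: those who only stop the device would lose their data, while those who leave altogether would keep theirs.
- **Deviators are already excluded under rejection (iv).** This stands. There is no real contradiction for deviators, only a shared poor choice.
- **LOCF may be meant for missed visits only.** This is a possible reading, so LOCF is used here only as support.
- **Analysis sets belong in the statistical analysis plan.** Nothing is said to be missing. Two stated rules give opposite instructions, and one of them is unsound whatever another document adds.

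A reader might also infer a loss of power: 30 × 0.70 = 21 is exactly the stated minimum, so any further exclusions would take a group below it. The document does not support this. It does not define dropout, which may already include patients removed under the Follow-up rule. The termination and LOCF rules would keep some of the dropouts in the analysis. The number of additional deviators is given nowhere. Nor is it shown that keeping non-adherent patients would regain power, since they may dilute the effect.

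**Conclusion.** The contradiction holds on the text for eligible patients who stop for severe symptoms, a serious event or another health reason: one section removes their data and another keeps them. For deviators the sections largely agree, and the objection is to removing randomised patients at all. Followed as written, the Follow-up rule can bias the VAS comparison, because it excludes patients for reasons that can be related to the outcome.

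The bias cannot be given a size or a sign. That would need the reasons for stopping by group and the VAS values of those who stopped, and the document has neither. The conclusion assumes only that the Follow-up sentence means what it says.

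A reader might infer from Trial status, which reports 45 completers by the end of 2017, that patients have already been lost to this rule. That figure does not show it; it only makes a check worthwhile. The text should be changed.

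**What to change.** 1. Delete the last sentence of the Follow-up paragraph and keep the recording of reasons.
2. Continue to collect VAS at the scheduled visits after a patient stops or deviates, where the patient agrees.
3. State that the primary VAS analysis includes all randomised patients in the group assigned, using all their recorded data.
4. Restrict rejection (iii) and (iv) to a supportive per-protocol analysis. Judge improper use blind to group, from the run-hour monitors described under Design.
5. Before unblinding, check whether any patients have already been set aside under the Follow-up rule. If so, restore their recorded VAS.

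Rejection (i) and (ii), and whether LOCF is a good method for values still missing, are separate questions and are not settled here.

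The cost is a few changes of wording, one check of patients already handled, and continued contact with those who stop. Keeping non-adherent patients may dilute the estimated effect somewhat; the per-protocol analysis will show how the result differs without them. VAS values that were never collected cannot be recovered.

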### Intervention in the treatment group

The patients will operate an Atmosphere® air purifier (Amway China, Guangzhou, China) in their bedrooms. This air purifier contains a HEPA two-way filter (model number 101076CH) with an airflow velocity of 100/200 cubic feet/minute at a filtration rate of 6000/12,000 cubic feet/hour. This represents 4/8 air changes per hour in a typical bedroom measuring 15 × 12 × 8 ft. The air purifier will be placed in the bedroom of the patient. Instructions will be given for the units to be left running continuously. The patients must stay in their bedrooms at night for 4 weeks (> 8 h each day).

